#### Study hypotheses.

The primary hypothesis is that participants with neuropathic pain will exhibit altered axonal properties and excitability compared to those without neuropathic pain.

Secondary hypotheses we will test are:

1) Somatosensory subgroups will match nociceptor properties. The planned outcomes are comparisons between neurophysiological and sensory phenotype variables, for example, mechanical hyperalgesia sensory profile will show lowered neurophysiological threshold to mechanical stimulation.2) Genetic variants will confer a unique nociceptive axonal profile and excitability signature. The planned outcome is the comparison of nociceptor fibre excitability and axonal properties between those participants with and without genetic variants.

#### Statistical plan.

Analyses will address the relationships between neuropathy, neuropathic pain, quantitative sensory phenotype and microneurography measures of nociceptor excitability and axonal properties. Analyses will be prespecified, scripted for reproducibility and conducted using appropriate statistical software.

Continuous variables will be summarised using mean (standard deviation) or median (interquartile range) depending on distribution; categorical variables will be summarised using counts and percentages. Point estimators will be reported alongside their respective 95% confidence interval. All hypothesis tests will be two-tailed. Where multiple comparisons are performed, p-values will be adjusted using methods appropriate to the comparison (for example Bonferroni or false discovery rate), and this will be reported alongside unadjusted p-values.

The primary hypothesis is that participants with neuropathic pain will exhibit altered axonal properties and excitability compared to those without neuropathic pain. The primary outcome will therefore be a comparison of microneurography measures of axonal excitability and axonal properties between participants with and without neuropathic pain.

#### Primary outcome comparisons.

Comparison of mean values and distributions of axonal excitability and axonal property measures at participant level for individual nociceptive fibres (for example, spontaneous activity, multiple spikes, mechanical and thermal sensitisation, conduction velocity, and activity-dependent slowing).

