**Methods and analysis:**

We will conduct an observational controlled study at the University of Oxford (2022–2029) following STROBE guidelines. Adults with and without neuropathy or neuropathic pain will undergo deep phenotyping, including questionnaires, neurological examination, quantitative sensory testing, nerve conduction studies, microneurography, skin biopsy, and genetic and transcriptomic analyses. Microneurography recordings will quantify C-fibre axonal properties, excitability, spontaneous activity, and responses to electrical, thermal, and mechanical stimulation. Participants will be stratified by neuropathy grade, neuropathic pain status, somatosensory phenotype, and genetic variants. Primary analyses will compare axonal excitability and related microneurography measures between participants with and without neuropathic pain. Secondary analyses will evaluate the associations between microneurography-derived nociceptor functional profiles and quantitative sensory phenotypes, and will assess the impact of rare ion-channel variants on C-fibre excitability. Multivariable regression, dimensionality reduction, and unsupervised clustering methods will be applied to delineate mechanistically informed patient subgroups.

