### Specialised investigations

#### Microneurography.

Microneurography records single-unit activity from peripheral sensory nerves in awake participants by inserting a microelectrode into a peripheral nerve [54]. We typically use the superficial peroneal nerve on the dorsum of the foot because it is superficial, purely sensory, anatomically relevant to distal symmetrical polyneuropathy, and generally well tolerated. It is also the most distal nerve available, which provides an advantage for length-dependent (‘dying-back’) neuropathies that show a distal-to-proximal gradient. In older participants (>70 years) or those with severe neuropathy where the superficial peroneal nerve is denervated or inaccessible, alternative sites (superficial radial nerve or more proximal peroneal sites) will be used.

C-fibres are characterised by the phenomenon of activity-dependent slowing of conduction velocity in response to repetitive transcutaneous electrical stimuli, and natural stimulation in a series of experiments [24].

The core protocol will consist of:

Identification of C-fibres at 0.25 Hz stimulation. After identification, stimulation is paused for three minutes to allow baseline recovery, followed by six minutes at 0.25 Hz. The rate is then increased to 2 Hz for three minutes and followed by a further six minutes at 0.25 Hz. The pause and 0.25 Hz blocks may be adjusted for participant tolerability, but the 2 Hz block will not be shortened.

Where possible this will be followed by the extended protocol.

Stimulation at 0.125 Hz, 0.25 Hz, 0.5 Hz and 1 Hz for at least two minutes at each frequency.Paired-pulse testing to assess recovery cycles by delivering a test stimulus at progressively shorter intervals after a conditioning stimulus.Mechanical and thermal natural stimulation of the receptive field using von Frey hairs and thermal probes (40°C, 45°C, 48°C and 20°C) to determine transduction thresholds and sensitisation to mechanical and thermal stimulation.

We aim to record from up to three independent receptive fields per participant, but a single stable recording suffices for inclusion. All C-fibres will undergo the core protocol; the extended protocol is optional and recorded whenever feasible.

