C-fibre subtypes are classified according to their response to an increase in electrical stimulation frequency to 2 Hz. This response, known as activity-dependent slowing of conduction velocity, is a characteristic feature of C-fibres in which conduction latency increases (i.e., slows) following repetitive stimulation. Using this method, five distinct populations of C-fibres can be identified: type 1A (“mechano-sensitive”) nociceptors, type 1B (“mechano-insensitive”) nociceptors, cold thermoreceptors, low-threshold mechanoreceptors, and cutaneous sympathetic efferent fibres [24,25].

There are two main reasons for distinguishing between a core and an extended recording protocol. The first relates to participant tolerability. Some individuals, particularly older participants, find prolonged recordings difficult due to musculoskeletal discomfort, difficulty keeping the limb still, challenges in following instructions, or urinary urgency. To minimise discomfort, participants are seated in a supportive chair with pillows to cushion pressure points, and are offered comfort breaks at the start of the recording. The second reason concerns recording stability. C-fibre signals may be lost during longer sessions because of small movements of the electrode or limb, or loss of contact during natural stimulation. As a result, extended recordings cannot always be completed. To prevent ascertainment bias, data from the extended protocol will therefore be treated as secondary or exploratory outcomes.

Microneurography measurements will include measures of:

Axonal properties

i. Baseline conduction velocity.ii. Degree of activity-dependant slowing to several stimulation frequencies (e.g., 0.25 Hz to 2 Hz)iii. Action potential morphology analysis of the extracellular recorded action potentialsiv. Threshold responses to thermal and mechanical stimulation

Nociceptor excitability

i. Spontaneous activityii. Double or multiple spikesiii. Thermal and mechanical sensitisation defined as prolonged ongoing discharges outlasting stimulus duration or lowered thresholds in response to thermal and mechanical stimulation.

Axonal excitability (across all C-fibre types)

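### The primary comparisons name mechanical and thermal sensitisation, which only the optional extended recording yields, although the plan makes extended-recording data secondary or exploratory

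*Protocol article*

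**What the plan says.** The Microneurography section describes two recordings. The core protocol, which every C-fibre undergoes, is electrical stimulation only: a 0.25 Hz search, a pause, and 0.25 Hz again. "The rate is then increased to 2 Hz for three minutes and followed by a further six minutes at 0.25 Hz". The extended protocol is optional and done where it can be. It holds further stimulation frequencies, "Paired-pulse testing to assess recovery cycles by delivering a test stimulus at progressively shorter intervals after a conditioning stimulus", and "Mechanical and thermal natural stimulation of the receptive field using von Frey hairs and thermal probes".

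The same section explains that extended recordings cannot always be finished, because some participants do not tolerate them and because signals are lost. It draws the consequence that "data from the extended protocol will therefore be treated as secondary or exploratory outcomes". Strengths and limitations agrees: it mentions incomplete extended recordings only as a threat to secondary measures.

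The Statistical plan states: "The primary outcome will therefore be a comparison of microneurography measures of axonal excitability and axonal properties". The abstract puts it similarly: "Primary analyses will compare axonal excitability and related microneurography measures between participants with and without neuropathic pain". Primary outcome comparisons then illustrates the measures: "for example, spontaneous activity, multiple spikes, mechanical and thermal sensitisation, conduction velocity, and activity-dependent slowing".

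**The concern.** The authors saw that completion of the extended recording is selective and set a rule to keep its data out of the primary outcome. The primary list then includes a measure that only that recording can supply.

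The reasons given for non-completion are older age, discomfort, difficulty keeping still or following instructions, urinary urgency and loss of signal, including loss during natural stimulation itself. Missing sensitisation data are therefore unlikely to be missing completely at random. Neither the participant-level averages nor the Mann–Whitney or t-tests under Planned primary analysis correct for who completed the step. If completion is related to pain status or to how the fibre responds, a primary comparison of sensitisation would carry the bias that the rule was written to avoid. Two analysts following different sections would also report different primary results.

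**Working it through.** No formula applies, and the plan states no figure to reproduce. The check traces each measure to the recording step that yields it and compares the result with the rule for extended data.

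**Measures named under Primary outcome comparisons**

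| Measure | What it needs | Recording | Fits the rule as primary? |
|---|---|---|---|
| Conduction velocity | Electrical stimulation at baseline | Core | Yes |
| Activity-dependent slowing | Change from 0.25 to 2 Hz | Core (0.125, 0.5 and 1 Hz are extended) | Yes, for 0.25 to 2 Hz |
| Spontaneous activity | No natural stimulus or paired pulse | Core | Yes |
| Multiple spikes | No natural stimulus or paired pulse | Core | Yes |
| Mechanical and thermal sensitisation | Response to mechanical or thermal stimuli | Extended only | No |

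The article does not tie spontaneous activity or multiple spikes to a particular step. They are placed under core because nothing in their description calls for an extended one. Sensitisation is different. The Microneurography section defines it by discharge that outlasts a stimulus or by lowered thermal and mechanical thresholds, and gives measuring it as a purpose of the extended natural-stimulation step.

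**Domains named in the Statistical plan, read against the Microneurography headings**

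- *Axonal excitability* has one item, the velocity recovery cycle. It is obtained by paired pulses, which are extended only.
- *Axonal properties* has four items. One of them, thresholds to thermal and mechanical stimulation, is extended only.
- *Nociceptor excitability* holds spontaneous activity, double or multiple spikes, and sensitisation. The Statistical plan's outcome sentence does not name this heading, yet Primary outcome comparisons draws its examples partly from it.

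So one named primary measure contradicts the rule outright. In addition, the domain labels in the outcome sentence, taken by their own headings, would admit two more extended-only measures and leave out two core ones (spontaneous activity and multiple spikes).

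**What can be sized.** Sample size justification allows 124 × 0.60 + 148 × 0.80 = 74.4 + 118.4 = 192.8, about 193 participants with a successful recording. The arithmetic stops there: no proportion completing the extended protocol is given, nor the split of those participants by pain status.

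**The case against.** The strongest defence has four parts.

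- *The list is only illustrative.* It is introduced as examples, and the governing rule is explicit and repeated in substance under Strengths and limitations. Even so, an example of a primary measure is still called primary, and this one cannot be primary under the rule.
- *The analysis plan will settle it.* Risk of bias and mitigation promises a pre-specified, published plan, and a closed list may properly sit there. That answers a complaint about missing detail. It does not reconcile two current statements that conflict.
- *Adjustment helps.* Age is a covariate in the logistic models. The simple between-group tests do not use it, and age is only one of the stated reasons for non-completion.
- *Relabelling does not remove selective missingness.* This stands. Moving sensitisation to secondary lowers the weight placed on it but does not make the data complete.

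A reader might also infer more than the article supports:

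- *That the leading primary construct is wholly extended-only.* Primary outcome comparisons never names the recovery cycle and uses axonal excitability loosely for measures filed elsewhere as nociceptor excitability. This shows inconsistent terms; it does not show that the recovery cycle was meant to be primary.
- *That a definite share of the primary family is affected, with a definite change in a Bonferroni threshold.* The list has five comma-separated items, or six if mechanical and thermal sensitisation are counted separately. It is open-ended, and false discovery rate control is offered as an alternative, so no family size is fixed.
- *That a stated loss of power follows.* Any detectable difference would rest on an assumed completion rate and an assumed split by pain status. Core measures would not lose participants in any case.
- *That completion differs by pain status.* The article does not say so.
- *That the primary hypothesis must be reworded.* It already refers to axonal properties and excitability in general, and the mechanical-threshold example under Study hypotheses is already secondary.

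**Conclusion.** The contradiction is certain, and it is narrow. Mechanical and thermal sensitisation is listed among the primary comparisons, while the plan's own rule makes the data it comes from secondary or exploratory. The other four named measures are unaffected, provided that activity-dependent slowing means the 0.25 to 2 Hz change. The domain wording in the Statistical plan and abstract is a related ambiguity that the same edit can clear.

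The conclusion rests on the text alone and needs no numerical assumption beyond the reading that spontaneous activity and multiple spikes are available from the core recording. The size of any bias, loss of power or effect on multiplicity cannot be derived from the article and is not claimed. The point still deserves correction, because it decides which measures count as primary and restores a safeguard that the authors chose themselves.

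**What to change.** 1. Under Primary outcome comparisons, replace the examples with a list limited to core-protocol measures: baseline conduction velocity, activity-dependent slowing from 0.25 to 2 Hz, spontaneous activity, and double or multiple spikes.
2. State that mechanical and thermal sensitisation, thermal and mechanical thresholds, and the velocity recovery cycle are secondary or exploratory. When they are reported, give the number of participants in each pain group who completed the relevant step.
3. Align the outcome sentence in the Statistical plan and the matching sentence in the abstract with the Microneurography headings, for example *axonal properties and nociceptor excitability*, restricted to core measures.
4. Leave Study hypotheses as it is.

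The cost is wording in the protocol and analysis plan, with whatever amendment approval and registration the study's own procedure requires. No recording changes, and the extended data are still collected and analysed. Recruitment began in February 2022 and data collection runs to September 2029, so the change can be made before the final analysis. It should be dated and made without reference to results by pain group.

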#### Planned primary analysis.

Between-group comparisons (neuropathic pain vs no neuropathic pain) will be conducted using appropriate non-parametric tests (Mann–Whitney U test) where data are not normally distributed, or independent-samples t-tests where normality is satisfied.

Data from individual nociceptive fibres will be analysed with explicit consideration of clustering within participants. Where appropriate, fibre-level measurements will be summarised at the participant level (for example, by averaging) to provide an independent observation per participant for primary analyses. In addition, mixed-effects models will be used, with participant included as a random effect, to account for within-participant variability. Multiplicity arising from multiple outcomes will be addressed using appropriate multiple-comparison adjustments (for example, Bonferroni or false discovery rate correction).

This dual approach allows us to perform conservative primary analyses at the participant level by averaging, while also utilising more sophisticated modelling through a mixed-effects model that retains the detail of the individual fibre data while correcting for the dependence between fibres from the same participant. The mixed-effects model will bridge the participant (unit of inference) and individual fibre (unit of observation) without the statistical error of treating fibres from the same person as independent data points.

Multivariable logistic regression models will be used to examine the association between neuropathic pain status and microneurography-derived measures of axonal excitability and properties, adjusting for prespecified covariates (age, sex, diabetes status, neuropathy severity, and medication use).

Multicollinearity among predictors will be evaluated using variance inflation factors; when two predictors are highly correlated, the variable with greater variance or stronger biological relevance will be retained in the final model.

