#### Sample size justification.

Sample size calculations are based on power to identify differences in QST cluster frequencies and to support clustering and multivariate analyses.

- Using pilot quantitative sensory testing data from DOLORisk, expected cluster frequencies for diabetic distal symmetrical polyneuropathy are 53.9% (sensory loss), 25.0% (mechanical hyperalgesia) and 15.8% (thermal hyperalgesia). For non-diabetic neuropathies the corresponding frequencies are 49.7%, 21.2% and 14.5%.

- For moderate effects (Cohen’s d ~ 0.5) in the quantitative sensory testing cluster analyses, a total of 130 diabetic and 148 non-diabetic participants provides approximately 80% power at α = 0.05.

- For k-means and hierarchical clustering applied after principal component analysis, a conservative estimate requiring 2^8 = 256 participants was used to ensure adequate representation across variable permutations.

- A multivariate regression model with age, sex, diabetes status, neuropathy severity, and medication use will require 8 degrees of freedom to represent all its variables (assuming a categorical variable coding for 4 categories of medication). Allowing for at least 15 event per variable (EPV) we will require a sample size of at least 120 participants for model development. As described above, variable selection and filtering based on multicollinearity will likely increase the EPV.

- Taking these calculations together (and accounting for anticipated success rates in microneurography recordings: minimum 60% for diabetic participants and 80% for non-diabetic participants), the recruitment target is 272 participants (124 diabetic and 148 non-diabetic).

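### If family-wise control is used for the primary microneurography measures, Holm should replace Bonferroni as the named method: same error rate, never less power

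*Protocol article*

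**What the plan says.** The protocol article deals with multiplicity in two places.

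- Under Statistical plan, for multiple comparisons in general: "p-values will be adjusted using methods appropriate to the comparison (for example Bonferroni or false discovery rate". The same paragraph adds that "this will be reported alongside unadjusted p-values" and that "Point estimators will be reported alongside their respective 95% confidence interval".
- Under Planned primary analysis, for the primary outcomes: "Multiplicity arising from multiple outcomes will be addressed using appropriate multiple-comparison adjustments (for example, Bonferroni or false discovery rate correction".

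The primary measures appear under Primary outcome comparisons as an open list: "for example, spontaneous activity, multiple spikes, mechanical and thermal sensitisation, conduction velocity, and activity-dependent slowing". All are summarised per participant and compared between the two pain groups, and "All hypothesis tests will be two-tailed".

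The section on microneurography places natural mechanical and thermal stimulation in the optional extended protocol. It treats extended-protocol data as secondary or exploratory.

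**The concern.** Bonferroni tests every measure at α/m, where m is the number of measures. Holm tests the smallest p-value at α/m, the next at α/(m−1), and so on to α, and stops at the first failure. Its first threshold equals Bonferroni's and every later one is larger. It therefore rejects whatever Bonferroni rejects and sometimes more, and it holds the family-wise error rate under any dependence. For testing, Bonferroni is dominated.

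The primary hypothesis expects both axonal properties and excitability to differ with pain. Several measures may then differ together, which is where a step-down method gains most. The article gives no power for the primary comparison at any adjusted α, so an avoidable loss there is worth removing.

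**Working it through.** **The plan's own power figure.** The only one stated is for the sensory-testing clusters: "a total of 130 diabetic and 148 non-diabetic participants provides approximately 80% power at α = 0.05", at d about 0.5. Comparing sensory loss with the two hyperalgesia clusters pooled, and using the article's cluster frequencies, gives 78.4% (70 v 53 diabetic) and 79.2% (74 v 53 non-diabetic). The figure can thus be reproduced under one plausible reading, although the article names no formula. It does not concern the primary comparison, so the power below is assumed.

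**Inputs**

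- α = 0.05, two-sided (Statistical plan; Sample size justification).
- m = 6 if each named measure counts once, 5 if mechanical and thermal sensitisation count as one, and 4 if both are left out as extended-protocol data.
- Assumed: 80% unadjusted power per true effect, so the non-centrality is 1.960 + 0.842 = 2.802.
- Assumed: equal correlation of 0, 0.3 or 0.6 between test statistics. The article states none.

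**Bonferroni**, in closed form: power = Φ(2.802 − z), where z is the two-sided critical value at 0.05/m.

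- m = 4: Φ(2.802 − 2.498) = 61.9%
- m = 5: Φ(2.802 − 2.576) = 58.9%
- m = 6: Φ(2.802 − 2.638) = 56.5%

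**Holm**, by simulation (400,000 replicates per scenario). Gain over Bonferroni per true effect, in percentage points, over the three correlations:

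| True effects | m = 4 | m = 5 | m = 6 |
|---|---|---|---|
| 1 | 0.0–0.2 | 0.0–0.1 | 0.0–0.1 |
| 2 | 2.1–2.6 | 1.6–1.9 | 1.3–1.5 |
| 3 | 4.8–5.8 | 3.6–4.1 | 2.8–3.2 |
| all m | 8.7–10.7 | 9.4–11.5 | 9.9–11.8 |

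Wherever some measures had no true effect, Holm's family-wise error was at most 0.046. The chance of at least one rejection was identical under both methods in every scenario, as it must be, because both start at α/m.

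**Second setting, from the recruitment figures.** Usable recordings: 124 × 0.6 + 148 × 0.8 = 74.4 + 118.4 ≈ 193. Assume a 1:1 pain split, m = 6, and d = 0.5 borrowed from the sensory-testing calculation. Non-centrality = 0.5 × √(193/4) = 3.473, so Bonferroni power is Φ(3.473 − 2.638) = 79.8%. Simulated power per true effect:

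| True effects of 6 | Bonferroni | Holm | Benjamini–Hochberg |
|---|---|---|---|
| 1 | 80% | 80% | 80% |
| 3 | 80% | 82–83% | 88–89% |
| 6 | 80% | 88–91% | 92–93% |

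Benjamini–Hochberg controls the false discovery rate. Its family-wise error reached 0.09 in these runs, so it does not replace Holm where family-wise control is wanted.

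**The case against.** The strongest reply is that the protocol has not chosen Bonferroni. It promises an appropriate adjustment and offers Bonferroni as one example beside false discovery rate, so Holm already fits the wording. The analysis plan, which is not shown, would normally fix the method. This stands, and it limits the point to an improvement of the named example.

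A reader might infer that the plan is bound to Bonferroni and throws real effects away for nothing. The documents do not support that. The loss arises only if Bonferroni is finally used. False discovery rate is an equal alternative and has at least as much power as Holm in the settings above. Unadjusted p-values, estimates and intervals will be shown whatever the adjustment, although they do not restore power to the adjusted test.

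A reader might also infer that correlation between the measures is the reason for Holm. It is not: Holm ignores correlation. A Westfall–Young step-down uses it, but simple permutation of pain labels does not suit the covariate-adjusted models that the article also plans, because it breaks the link between pain and the covariates.

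Bonferroni does give simple simultaneous intervals that match its tests, and Holm does not. The plan makes no use of this, since it reports ordinary 95% intervals.

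**Conclusion.** The point holds as a low-severity, cost-free improvement. If family-wise control is used for the primary family, Holm gives the same guarantee as the one named method and never has less power. With four to six measures at 80% unadjusted power, the gain per true effect is about 0 points with one true effect, 1 to 3 with two, 3 to 6 with three, and 8 to 12 when all are true. There is no gain in the chance of at least one finding.

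These sizes rest on the assumed family, power and correlation; that Holm is never worse rests on none of them. If false discovery rate is the chosen criterion, the point does not arise.

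**What to change.** Under Statistical plan and Planned primary analysis, name Holm in place of Bonferroni as the family-wise method for the primary family. Report Holm-adjusted p-values next to the unadjusted ones already promised. Holm needs only p-values, so it serves the participant-level tests, the mixed-effects models and the adjusted regressions alike. A Westfall–Young step-down is best left out, or limited to the unadjusted participant-level comparisons with pain status permuted across participants and not across fibres.

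The cost is a change of wording in the protocol or analysis plan. No participants, recordings or tests are added, and the family-wise error rate is the same. Data collection runs to September 2029, so the change can be made before analysis.

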#### Secondary analyses.

Secondary hypotheses explore relationships between somatosensory phenotype (QST clusters), genetic variants and nociceptor excitability signatures.

1. Somatosensory subgroup correspondence

- Compare microneurography variables across QST-defined phenotypic groups (sensory loss; mechanical hyperalgesia; thermal hyperalgesia) using non-parametric ANOVA (Kruskal–Wallis) or one-way ANOVA as appropriate.

- If omnibus tests are significant, perform post-hoc comparisons with correction for multiple testing.

2. Genetic variant effects

- Compare microneurography measures between participants who carry rare variants in ion channel genes (NaV, TRPA1) and those who do not, stratified by aetiology (diabetic versus non-diabetic).

- Use regression models to estimate the effect of genetic variants on fibre excitability, adjusting for confounders. If sample sizes for specific variants are small, present descriptive statistics and cautionary interpretation.

3. Microneurography association analyses

- Spearman rank-order correlations will evaluate associations between microneurography measures and clinical metrics: spontaneous pain intensity, evoked pain intensity, DN4/NPSI descriptor scores, and quality-of-life measures.

- A binomial regression model will examine the association between microneurography variables and membership of somatosensory subgroups.

Dimensionality reduction and clustering

Given the high dimensionality of clinical, genetic, microneurographic and biochemical data, we will use dimensionality reduction and unsupervised clustering to identify latent patient subgroups.

- Apply principal component analysis to standardised variables across the domains of interest (genetics, demographics, microneurography, biochemistry). Retain components that explain an adequate cumulative variance (e.g., eigenvalues >1).

- Apply k-means, centroid and hierarchical clustering on retained principal components. Determine optimal cluster number using multiple metrics (gap statistic, silhouette width, elbow method).

- After cluster assignment, compare original variables across clusters using omnibus tests with post-hoc comparisons to characterise cluster profiles.

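### The collinearity rule for the adjusted logistic models uses a unit-dependent criterion and can remove a prespecified confounder

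*Protocol article*

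**What the plan says.** All references are to the protocol article.

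- **Planned primary analysis, the model.** Multivariable logistic regression examines the "association between neuropathic pain status and microneurography-derived measures of axonal excitability and properties". Pain status is the outcome. The fibre measures and the covariates are predictors, the models being described as "adjusting for prespecified covariates (age, sex, diabetes status, neuropathy severity, and medication use".
- **Planned primary analysis, the rule.** "Multicollinearity among predictors will be evaluated using variance inflation factors". Of a strongly collinear pair, "the variable with greater variance or stronger biological relevance will be retained in the final model". No predictor is exempt, and no order is given between the two criteria.
- **Primary outcome comparisons.** The measures are "spontaneous activity, multiple spikes, mechanical and thermal sensitisation, conduction velocity, and activity-dependent slowing", which have different natural units.
- **Secondary analyses.** Standardisation appears only for the multivariate step: "Apply principal component analysis to standardised variables across the domains of interest". It is not mentioned for the logistic models.
- **Sample size justification.** Eight degrees of freedom at 15 events per variable (EPV) give 120 participants. The text then adds that "variable selection and filtering based on multicollinearity will likely increase the EPV".

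**The concern.** The rule is stated as a decision, so an analysis plan that follows the article inherits it. It has two faults.

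First, the variance criterion has no bearing on which of two collinear predictors should stay. The choice can change when a variable is re-expressed in another unit. The alternative criterion does not settle the matter: where the two disagree, either choice complies with the text.

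Second, the rule makes no distinction between the fibre measures under study and the covariates adjusted for. A confounder that is strongly correlated with a fibre measure is the one whose adjustment matters most, and it is also the one the rule can remove. If it goes, its effect on pain is attributed to the fibre measure. That sits badly with the section on risk of bias, which promises that confounders will be adjusted for in the regression models.

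**Working it through.** **1. The plan's own figure.** 8 × 15 = 120, as stated. This is the only figure tied to the collinearity filter. In the plan's own counting, removing one degree of freedom moves the ratio from 120/8 = 15 to 120/7 = 17.1. Where the freed degree of freedom belongs to a listed covariate, the gain comes from giving up that adjustment.

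**2. Dependence on units.** For any constant c, Var(cX) = c²·Var(X), so going from m/s to cm/s multiplies a variance by 100² = 10,000. The check used one simulated data set of 193 participants. That number comes from the plan's recruitment targets and recording success rates: 124 × 0.60 + 148 × 0.80 = 74.4 + 118.4 = 192.8. The other inputs are assumptions that the article does not give: correlation 0.95, conduction velocity SD 0.15 m/s, and activity-dependent slowing SD 0.08 as a fraction.

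| Units (velocity; slowing) | Variance, velocity | Variance, slowing | Kept by variance |
|---|---|---|---|
| m/s; fraction | 0.0183 | 0.0058 | velocity |
| m/s; percent | 0.0183 | 57.7 | slowing |
| cm/s; percent | 182.6 | 57.7 | velocity |

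The variance inflation factor (VIF, 10.99) and the full-model log-likelihood (−125.41) are the same in every row. Only the units differ. The SDs are illustrative, but the algebra holds for any SD. With both variables standardised, both variances are 1 and the criterion cannot choose.

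The same applies to covariates. A 0/1 variable has variance p(1 − p) ≤ 0.25, so in raw units diabetes status or sex loses to most continuous variables. Age, with an assumed SD of about 12 years, had a simulated variance of about 167 in years and 1.67 in decades.

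**3. Consequence of dropping a confounder.** Assumptions: n = 193; neuropathy severity raises the log-odds of pain by 0.5 per SD; a fibre measure has no effect of its own but correlates with severity at r = 0.9. With two predictors, VIF = 1/(1 − r²) = 1/(1 − 0.81) = 5.3, a level at which such a rule could plausibly act.

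- Severity kept: the measure is significant in about 5% of simulated studies, as it should be.
- Severity dropped: about 82–85%, the range over repeated simulations of 800 to 1,500 studies.

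A hand check gives the same order of size. Without severity, the measure's coefficient is roughly 0.5 × 0.9 = 0.45 per SD. Its standard error is roughly 1/√(193 × 0.25) = 0.144. The ratio is 0.45/0.144 = 3.1, so power is about Φ(3.1 − 1.96) ≈ 0.87. This is slightly high because it ignores attenuation and uses the largest possible binomial variance.

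**The case against.** **The rule has a second criterion.** A reader might infer that units alone decide which measure survives. The text does not support that. Biological relevance does not depend on units, and an analyst could use it in every case and keep every confounder. But nothing requires this.

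**The main comparisons are untouched.** A reader might also infer that a primary measure could vanish from the study. It could not. The primary outcome is a between-group comparison by Mann–Whitney or t-test on participant-level summaries, supported by mixed-effects models, and the rule follows only the logistic models. This limits the point to the adjusted association.

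**The screening does not use the outcome.** It is tempting to say that final-model p-values are invalid because they ignore selection. VIFs and predictor variances do not involve pain status, so choosing by them does not in itself inflate type I error. The harm comes from omitting a confounder.

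**The sizes are assumed.** The article gives no correlation between severity and any fibre measure. At r = 0.75 or 0.8 the two-predictor VIF is only 1/(1 − 0.5625) = 2.3 or 1/(1 − 0.64) = 2.8, which may not trigger the rule, so those cases are not relied on here. The rule might also drop the fibre measure rather than the covariate, which does no harm through confounding. For two competing fibre measures, the share of simulated studies whose verdict depended on which was kept fell from about 10% at r = 0.9 to about 5–6% at r = 0.95, so that part matters less as collinearity rises.

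**One model per measure may be intended.** The article speaks of models in the plural. Under that reading, however, every collinear pair includes at least one listed covariate, so the rule would remove either a covariate or the very measure being tested.

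**The full analysis plan is not shown.** It may set a VIF cut-off or a scale, and their absence from the article is not held against it. The stated variance criterion and the lack of an exemption for the covariates are in the text as it stands.

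**Conclusion.** The point holds for the adjusted logistic models. The variance criterion depends on units and is empty after standardisation. The alternative criterion is undefined and unranked. The rule as worded can remove a covariate described as prespecified, and the sample size section, which lists only those covariates by name, expects such filtering.

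Under the stated assumptions at r = 0.9, losing a true confounder raises the false-positive rate for a null fibre measure from about 5% to about 82–85%. That figure shows what can happen if the rule acts on such a pair. It is not a forecast for this study, because both the correlation and the effect size are assumed and the rule is idle unless predictors prove highly correlated. The unadjusted comparisons and the mixed models stand regardless.

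**What to change.** 1. Delete the variance criterion.
2. State that age, sex, diabetes status, severity of neuropathy and medication stay in every adjusted model whatever their VIF, with VIFs reported as a diagnostic only.
3. Fit one adjusted model per fibre measure, so that collinearity among measures cannot remove one. If a joint model is wanted, write down the order in which measures are retained before analysis.
4. In the sample size justification, remove the statement that filtering for multicollinearity will raise the EPV, as far as it concerns these covariates.

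The cost is wording only, with no new data or participants. Intervals will be wider where a covariate is truly collinear with a measure: at r = 0.9 the standard error is about √5.3 = 2.3 times what it would be with an uncorrelated covariate. That width reflects how little the data can separate the two. Recruitment and data collection run to September 2029, so the change can be made before the final analysis.
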